#### Unadjusted prevalence

The evaluation of unadjusted prevalence uses a binomial GEE with logit link function. Village\_ID is treated as the repeated subject, and we assume compound symmetry within a village. 'Lsmestimate' is used to test the pre-specified differences between arms.

```
ods trace off;
proc genmod data=allyears descending;
  where Study_Year = 5;
  class Study_Arm Village_ID / param=glm;
  model Sh = Study_Arm / dist=bin link=logit ;
  repeated subject=Village_ID / type=cs;
  lsmeans Study_Arm / cl;
  lsestimate Study_Arm "arm 2 vs. arm 1" -1 1 0 0 0 0 / cl;
  lsestimate Study_Arm "arm 3 vs. arm 1" -1 0 1 0 0 0 / cl;
  lsestimate Study_Arm "arm 4 vs. arm 1" -1 0 0 1 0 0 / cl;
  lsestimate Study_Arm "arm 5 vs. arm 1" -1 0 0 0 1 0 / cl;
  lsestimate Study_Arm "arm 6 vs. arm 1" -1 0 0 0 0 1 / cl;

  lsestimate Study_Arm "arm 3 vs. arm 2" 0 -1 1 0 0 0 / cl;
  lsestimate Study_Arm "arm 4 vs. arm 2" 0 -1 0 1 0 0 / cl;
  lsestimate Study_Arm "arm 5 vs. arm 2" 0 -1 0 0 1 0 / cl;
  lsestimate Study_Arm "arm 6 vs. arm 2" 0 -1 0 0 0 1 / cl;

  lsestimate Study_Arm "arm 4 vs. arm 3" 0 0 -1 1 0 0 / cl;
  lsestimate Study_Arm "arm 5 vs. arm 3" 0 0 -1 0 1 0 / cl;
  lsestimate Study_Arm "arm 6 vs. arm 3" 0 0 -1 0 0 1 / cl;

  lsestimate Study_Arm "arm 5 vs. arm 4" 0 0 0 -1 1 0 / cl;
  lsestimate Study_Arm "arm 6 vs. arm 4" 0 0 0 -1 0 1 / cl;

  lsestimate Study_Arm "arm 6 vs. arm 5" 0 0 0 0 -1 1 / cl;
estimate "O.R. arm 2 vs. arm 1" Study_Arm -1 1 0 0 0 0 / exp cl;
run;
```

Adjusted prevalence

The code is the same as for unadjusted prevalence, but with age, sex, and a weighting for village size added to the model.

villweight of individual = 1/# samples collected in village

```
ods trace off;
proc genmod data=allyears descending;
  where Study_Year = 5;
  class Study_Arm Village_ID Sex Age / param=glm;
  model Sh = Study_Arm Sex Age / dist=bin link=logit ;
  repeated subject=Village_ID / type=cs;
  weight villweight ;
  lsmeans Study_Arm / cl;
run;
```

ICC of prevalence

```
/*macro*/
%macro icc_bin(data, cluster, outcome, out, m, stval=%str(), pred=%str());
proc nlmixed data=&data.;
  parms b0=0 &stval. var1=1;
  eta = exp(b0 + &pred. r);
  pred = eta / (1+eta);
  model &outcome. ~ binary(pred);
  random r ~ normal(0,var1) subject=&cluster.;
  estimate 'ICC' var1/(var1 + (constant('PI')**2)/3);
  estimate 'Deff' 1 + (&m.-1) * (var1/(var1 + (constant('PI')**2)/3));
  ods output AdditionalEstimates=&out.;
run;

data &out.;
  set &out.;
  cluster="&cluster.";
  outcome="&outcome.";
  m=&m.;
run;
%mend;
```

```
%icc_bin(sac, HHID, asc, hhl, 2.91, stval=%str(), pred=%str());
```

Unadjusted intensity

The code is the same as for unadjusted prevalence, but the distribution and link are changed.

```
ods trace off;
proc genmod data=allyears descending;
  where Study_Year = 5;
  class Study_Arm Village_ID / param=glm;
  model Sh = Study_Arm / dist=nb link=log ;
  repeated subject=Village_ID / type=cs;
  lsmeans Study_Arm / cl;
run;
```

Adjusted intensity

The code is the same as for the adjusted prevalence, but the distribution and link are changed.

```
ods trace off;
proc genmod data=allyears descending;
  where Study_Year = 5;
  class Study_Arm Village_ID Sex Age / param=glm;
  model Sh = Study_Arm Sex Age / dist=nb link=log ;
  repeated subject=Village_ID / type=cs;
  weight villweight ;
  lsmeans Study_Arm / cl;
run;
```

Figure 4. Village-level mean intensity by year, by arm.

Provide a line graph showing arithmetic mean intensity, by Year, by Arm.

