### c. Study design: Gaining and Sustaining studies

**Overview:** The Gaining and Sustaining studies are parallel cluster-randomized, open-label operational research trials of praziquantel MDA for control of prevalence and intensity of *Schistosoma* infections in endemic communities in Africa.

**Study Arms:** Study 1 has three study arms arranged as follows:

[figure not shown]

Study 2 for both species has six study arms arranged as follows:

[figure not shown]

Note that Arms 1, 2, and 3 in Study 1 correspond to Arms 4, 5, and 6 in Study 2. Holidays indicate years in which a village did not receive MDA with praziquantel. No testing of children was conducted during holiday years; otherwise, infected children would have required treatment, which would have precluded evaluation of the impact of MDA holidays.

Because six villages in Mozambique had their cross-sectional study arm re-assigned after randomization (see Appendix L for Protocol Deviations), the initial analysis of treatment outcomes will be “as treated.” Children included in analysis are those who are an “available case,” that is, someone who provided age and sex information and at least one slide for evaluation of infection status.

**Populations and expected sample size:** The goal of each country study was to enroll 25 eligible villages per study arm, and to monitor each village’s prevalence and intensity of *Schistosoma* infection (whether Sm or Sh) among a **random sample of 100 resident 9-12 year-old children each year**, starting before implementation of MDA (Year 1) and continuing through Year 5 (see study arm schema above). Nominal enrollment for each Study 1 was 75 villages, with 7,500 children tested each year. Nominal enrollment for Study 2 was 150 villages, with 15,000 children tested each year.

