**Table 4. Comparisons of prevalence and intensity at Year 5 among arms.**

This table describes the primary outcomes.

|                       | Unadjusted prevalence model estimate (CI) | Adjusted prevalence model estimate (CI) | Unadjusted intensity ratio (CI) | Adjusted intensity ratio (CI) |
|-----------------------|--------------------------------------------------|------------------------------------------------|----------------------------------------|--------------------------------------|
| Arm 1 v. Arm 4 |                                                  |                                                |                                        |                                      |
| Arm 1 v. Arm 2 |                                                  |                                                |                                        |                                      |
| Arm 1 v. Arm 3 |                                                  |                                                |                                        |                                      |

|                |  |  |  |  |
|----------------|--|--|--|--|
| Arm 4 v. Arm 5 |  |  |  |  |
| Arm 4 v. Arm 6 |  |  |  |  |

*General approach to analysis:* The general approach is to use GEEs to estimate differences between the arms in year 5 only. We will report unadjusted estimates – with just village and arm fitted in the model – and adjusted estimates – where sex and age are also included in the model, along with weighting for number of children who provided data, because not all villages were able to sample 100 9-12 year old children.

ICC will be calculated using mixed models consistent with the GEE setup in the primary analysis.

All models will be based on individual level data on 9-12 year old children only.

*Sample code:* The following codes are provided as examples. Different studies may require further modification of the code below or may require different approaches.

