## **APPENDICES**

- A. Harmonized Protocol for SCORE Gaining and Sustaining Control Studies
- B. Harmonized Protocol for SCORE Cohort Studies of Subtle Morbidity
- C. Protocol for the Redesigned Niger Study
- D. Data Elements Available for Analysis
- E. Data Dictionary for SCORE Gaining and Sustaining Control Studies
- F. Data Dictionary for SCORE Coverage
- G. Example of a Study Flow Diagram
- H. Protocol Deviations

**Supplemental Table S1:** SCORE's Kenya Gaining Control Study comparisons of *S. mansoni* infection prevalence and intensity among 9-12 year-old children between study arms at Year 5, adjusted for community level clustering effects, age, and sex

|                               | Prevalence Ratio         |              | Intensity Ratio   |      |
|-------------------------------|--------------------------|--------------|-------------------|------|
| Study Intervention Comparison | Adjusted PR (CI)         | p            | Adjusted AMR (CI) | p    |
| CCSS vs. CCCC                 | 0.59 (0.34, 1.03)        | 0.06         | 0.36 (0.10, 1.24) | 0.11 |
| CCHH vs. CCCC                 | 1.19 (0.76, 1.87)        | 0.44         | 0.88 (0.36, 2.18) | 0.78 |
| SSSS vs. CCCC                 | 0.73 (0.42, 1.28)        | 0.28         | 0.48 (0.18, 1.30) | 0.15 |
| SSHH vs. CCCC                 | 1.09 (0.69, 1.73)        | 0.71         | 0.99 (0.34, 2.87) | 0.99 |
| SHSH vs. CCCC                 | 1.23 (0.78, 1.95)        | 0.37         | 1.01 (0.34, 3.00) | 0.99 |
| CCHH vs. CCSS          | 2.03 (1.23, 3.34) | 0.005 | 2.44 (0.82, 7.27) | 0.11 |
| SSSS vs. CCSS                 | 1.25 (0.68, 2.27)        | 0.47         | 1.34 (0.42, 4.27) | 0.62 |
| SSHH vs. CCSS          | 1.85 (1.11, 3.09) | 0.02  | 2.75 (0.81, 9.35) | 0.10 |
| SHSH vs. CCSS          | 2.09 (1.26, 3.47) | 0.004 | 2.80 (0.80, 9.75) | 0.11 |
| SSSS vs. CCHH                 | 0.61 (0.37, 1.01)        | 0.06         | 0.55 (0.25, 1.21) | 0.14 |
| SSHH vs. CCHH                 | 0.91 (0.62, 1.35)        | 0.65         | 1.13 (0.46, 2.73) | 0.79 |
| SHSH vs. CCHH                 | 1.03 (0.70, 1.51)        | 0.88         | 1.15 (0.46, 2.86) | 0.77 |
| SSHH vs. SSSS                 | 1.49 (0.89, 2.49)        | 0.13         | 2.05 (0.78, 5.39) | 0.15 |
| SHSH vs. SSSS          | 1.68 (1.01, 2.80) | 0.045 | 2.08 (0.77, 5.63) | 0.15 |

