| SSHH vs. SSSS          | 1.73 (1.08, 2.77)           | 1.32 (0.66, 2.61)                 |
| SHSH vs. SSSS                 | 1.12 (0.62, 2.02)                  | 0.70 (0.32, 1.53)                 |

Abbreviations: C, communitywide treatment; H, praziquantel holiday – a year when no praziquantel MDA was provided; S, school-based treatment.

**Bold** font indicates statistically significant differences.

**Supplemental Table S4:** SCORE's Kenya Sustaining Control Study comparisons of *S. mansoni* infection prevalence and intensity among 9-12 year-old children between study arms at Year 5, adjusted for community level clustering effects, age, and sex

|                               | Prevalence Ratio  |      | Intensity Ratio          |             |
|-------------------------------|-------------------|------|--------------------------|-------------|
| Study Intervention Comparison | Adjusted PR (CI)  | P    | Adjusted AMR (CI)        | p           |
| SSHH vs. SSSS                 | 1.49 (0.92, 2.39) | 0.10 | 1.62 (0.83, 3.15)        | 0.16        |
| SHSH vs. SSSS                 | 1.10 (0.72, 1.67) | 0.66 | 0.86 (0.47, 1.60)        | 0.64        |
| SHSH vs. SSHH          | 0.74 (0.48, 1.13) | 0.17 | 0.53 (0.29, 0.98) | 0.04 |

Abbreviations: AMR, arithmetic mean ratio; H, praziquantel holiday – a year when no praziquantel MDA was provided; PR, prevalence ratio; S, school-based treatment.

**Bold** font indicates statistically significant differences.

**Supplemental Table S5:** SCORE's Côte d'Ivoire Sustaining Control Study comparisons of *S. mansoni* infection prevalence and intensity among 9-12 year-old children between study arms at Year 5, adjusted for community level clustering effects, age, and sex

|                               | Prevalence Ratio  | Intensity Ratio   |
|-------------------------------|-------------------|-------------------|
| Study Intervention Comparison | Adjusted PR (CI)  | Adjusted AMR (CI) |
| SSHH vs. SSSS                 | 1.96 (0.88, 4.35) | 1.41 (0.41, 5.0)  |
| SHSH vs. SSSS                 | 1.85 (0.78, 4.35) | 1.96 (0.55, 7.14) |
| SHSH vs. SSHH                 | 0.94 (0.58, 1.54) | 1.39 (0.85, 2.27) |

*Abbreviations:* AMR, arithmetic mean ratio; H, praziquantel holiday, a year when no praziquantel MDA was provided; PR, prevalence ratio; S, school-based treatment.

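### The Table 4 sample code makes no small-sample correction for contrasts of about 25 versus 25 villages: a minor problem for prevalence, a material one for intensity

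*Combined protocol and SAP*

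**What the plan says.** In section VI.b of the harmonised SAP, Table 4 carries the primary outcomes. "The general approach is to use GEEs to estimate differences between the arms in year 5 only". Prevalence is binomial with a logit link; intensity is negative binomial with a log link. Both models cluster on village through "repeated subject=Village_ID / type=cs", and the accompanying text says that "we assume compound symmetry within a village". The code contains no option for a small-sample variance or for a t reference.

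On size, section II.c says "The goal of each country study was to enroll 25 eligible villages per study arm", each monitored through a "random sample of 100 resident 9-12 year-old children each year". Section VI.a lists the pre-specified contrasts (five for Study 2, two for Study 1) and leaves p-value cut-offs unadjusted. The Table 4 text introduces the code as an example that a study may need to modify. The preface allows other software, but asks that the SAP's definitions and approaches be used and that publications agree with them.

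**The concern.** A sandwich variance is estimated from the spread of village results, so its reliability depends on the number of villages, not of children. With about 25 per side it is biased low, and normal limits ignore its sampling error. Both faults make intervals too narrow. Egg counts make this worse: a few heavily infected villages can dominate an arithmetic mean, and a sample that misses them understates both the mean and the spread. With no multiplicity adjustment planned, nothing absorbs the excess. What is at stake is whether the 95% intervals and 5% tests for the primary outcomes mean what they say.

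**Working it through.** **Inputs.** 25 villages per arm and 100 children per village (section II.c; targets, since the analysed numbers are not given). Model and code from section VI.b. Reported intervals from Supplemental Tables S1-S5. The documents give no ICC, between-village CV, power or expected interval width. Assumed here: ICC 0.05-0.30 and village-mean CV 0.5-2.5.

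**The plan's own figures.** 25 × 6 = 150 villages and 150 × 100 = 15,000 children for Study 2; 25 × 3 = 75 and 75 × 100 = 7,500 for Study 1. Both agree with section II.c.

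**Near-normal case.** With arm as the only covariate, K equal villages per arm and village means m_i, the sandwich variance of an arm mean m̄ is Σ(m_i − m̄)²/K², carried to the log or logit scale by the delta method. A six-arm exchangeable GEE reproduced this exactly (SE 0.23354 both ways). Here the Kauermann-Carroll (KC) correction multiplies the SE by √(25/24) = 1.0206 and Mancl-DeRouen (MD) by 25/24 = 1.0417. The 97.5% t quantile is 2.0106 on 50 − 2 = 48 df and 1.9766 on 150 − 6 = 144 df, against 1.960. The widening needed is:

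| | 48 df | 144 df |
|---|---|---|
| KC | 4.7% | 2.9% |
| MD | 6.9% | 5.0% |

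**Simulation.** 25 versus 25 villages of 100 children, no true difference, 20,000 trials per setting. Infection was beta-binomial; egg counts were negative binomial around lognormal or gamma village means. Rejection rates at nominal 5%:

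| Setting | Sandwich, z | KC, t(48) | MD, t(48) |
|---|---|---|---|
| Prevalence 10% | 6.3-7.5% | 5.2-6.5% | 4.8-6.1% |
| Prevalence 20% | 5.9-6.2% | 4.9-5.1% | 4.4-4.8% |
| Prevalence 5% | 6.7-11.1% | 5.5-9.5% | 5.1-8.9% |
| Intensity, CV 0.5 | 6.6-7.2% | 5.5-5.9% | 5.0-5.3% |
| Intensity, CV 1.0 | 7.8-8.5% | 6.6-7.2% | 6.1-6.7% |
| Intensity, CV 1.8 | 10.4-11.6% | 8.9-9.8% | 8.3-9.1% |
| Intensity, CV 2.5 | 12.5-13.4% | 10.8-11.8% | 10.0-11.2% |

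A separate simulation of the same design gave about 6-7% for prevalence, about 8-11% for intensity at CV 0.9-1.9 and 13% at CV 2.9. A village-level randomisation test held 5.0-5.4% where the z test gave 8.9-13.1% (4,000 runs, 499 permutations).

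**Which CV is plausible?** If a reported interval is a sandwich interval with 25 villages per arm and equal CV in both arms, SE = ln(upper/lower)/3.92 and CV = SE × √(25/2) = 3.536 × SE. For the pre-specified intensity contrasts in S1-S5, the smallest value is S4 SHSH vs SSSS: ln(1.60/0.47)/3.92 = 0.313, CV 1.1. The largest is S5 SHSH vs SSSS: ln(7.14/0.55)/3.92 = 0.654, CV 2.3.

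**Illustration.** Kenya Sm2, SHSH vs SSSS prevalence (S1): 1.68 (1.01, 2.80), p = 0.045. ln 1.68 = 0.5188; SE = ln(2.80/1.01)/3.92 = 0.2601; z = 1.994, p = 0.046, which agrees with the table within rounding. The corrected limits are exp(0.5188 ± t × factor × 0.2601):

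| | Limits | p |
|---|---|---|
| KC, 144 df | 0.994, 2.84 | 0.053 |
| KC, 48 df | 0.985, 2.87 | 0.057 |
| MD, 144 df | 0.983, 2.87 | 0.057 |
| MD, 48 df | 0.974, 2.90 | 0.061 |

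**The case against.** For Table 4 the SAP names neither the variance estimator nor the reference distribution; sandwich estimators are named only in the cohort section (VII.b). The reading above rests on software defaults in code offered as an example. That stands as a limit on certainty. But the code is the only specification of these choices in the text supplied (Appendix H, the initial analysis plan, is not included), and the preface asks that the SAP's approaches be followed.

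Section VI.a also discloses the unadjusted cut-offs and bases interpretation on the strength of effects. That concerns multiplicity and does not widen an interval that is too narrow.

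A reader might infer four stronger things that the documents do not support:

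- That compound symmetry is the fault. The sandwich variance is robust to the working correlation.
- That both outcomes are affected alike. For prevalence of 10-30% the excess is only 1-2 points.
- That the bolded S4 intensity result, SHSH vs SSHH, 0.53 (0.29, 0.98), also falls. It is Arm 3 vs Arm 2, not a pre-specified contrast, and with KC and 75 − 3 = 72 df it stays at p = 0.049.
- That S1-S5 were produced by this code and must all be re-issued. They report prevalence ratios, whereas the logit code yields odds ratios, so their model and variance are unknown. S2 and S5 mark no significant result, and both bolded Mozambique results keep KC, t(48) lower limits of about 1.06-1.07.

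**Conclusion.** The point holds for the code as written. For prevalence it is minor: about 6-7% in place of 5% at prevalence 10-30%, though worse near 5% prevalence. For intensity it is material: about 8-11% at village CV 0.9-1.9 and about 13% at 2.5-2.9. A corrected variance with a t reference nearly repairs prevalence but leaves intensity at about 6-12% for CV 1.0-2.5, so intensity needs a second measure.

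The Kenya Sm2 contrast is an illustration only. It is the one pre-specified contrast in bold in S1; p is about 0.05-0.06 under each correction tried, so it should be called borderline.

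The sizes assume 25 equal villages per arm, the unadjusted model, and the stated ICC and CV ranges. They omit the village weight and the cap of 1,000 on egg counts, which would limit skew. The implied CVs assume that the published limits are sandwich intervals.

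**What to change.** In the Table 4 models, name one bias-corrected sandwich variance in advance (Kauermann-Carroll or Mancl-DeRouen) and a t reference on villages minus arms. Say whether the count covers the two arms compared (48 at target size) or all arms (144 or 72). In the arm-only model a pairwise sandwich variance uses only the two arms' villages, so 48 is the more cautious choice.

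For the pre-specified intensity contrasts, add a p-value from a randomisation test that re-allocates whole villages between the two arms. It must follow the allocation actually used. The protocol stratifies Study 2 by screening prevalence while SAP section II.a describes unstratified randomisation, so settle this first. In Mozambique, where six villages changed arm, use the original allocation.

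Re-run the pre-specified contrasts on this basis and describe Kenya Sm2 SHSH vs SSSS prevalence as borderline. The cost is a little more code and slightly wider intervals.

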## **VIII. PROTOCOL DEVIATIONS AND OTHER ISSUES**

A full listing of known protocol deviations is in Appendix L. One important issue relates to an underlying premise in the original design of the Sm2 and Sh2 studies, i.e., that well-conducted CWT would yield higher overall SAC treatment coverage and would prove more effective than other approaches. In Kenya, however, the CWT intervention in Year 1 was less intense than in the SBT arms because schools were not

used as treatment venues by the study teams. This will be commented on in the discussion of results but not adjusted for.

A second important issue of concern is that testing and MDA were supposed to occur on an annual basis. In some study locations, the agreed-to testing and treatment schedule was not reliably followed. A variable has been created to flag villages in which this occurred.

Several issues have arisen during the collection of the SCORE datasets. These include:

- Limited enrollment in some villages: The target study population size was 100 9-12 year old children. In some villages, the enrollment was significantly less. To account for this, a “village-weight” term will be added to the GEE model to weight results according to numbers of children tested per village.
- Truncation of Kato-Katz egg counts: In Kenya Sm1 and Sm2, egg counts were truncated at 42 eggs per slide in Years 1-3; they were truncated at 1,000 subsequently, which is more consistent with the laboratory practice used in other Sm clinical studies. We will not attempt to model the “true” egg counts for children with results recorded at the truncation level. We will present results indicating the recorded egg values and calculated egg values, and also categorized as no infection, and low, medium, or high-intensity infections.
- Missing data on some children
  - Children without data on age, sex, and presence or absence of eggs on at least one slide were not included in the study, with the exception of Mozambique, where 52 children (.9% of the total tested) are missing sex data in Year 1, and a smaller number are missing such data in later years. Children with missing sex data in Mozambique are largely from one village.
  - Issues related to some children having fewer slides than required by the protocol have been discussed elsewhere.
- Missing data are an issue for a limited number of variables in the cohort. This is discussed previously.

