### Figure 3. Intensity categories, by Arm, by Year.

This is a stacked bar chart, showing low, medium, and high intensity infections, by Arm, for Years 1-5, and each study separately. Intensity categories are defined as:

- Sh: Low 1-50 eggs/10 ml, high  $\geq 51$  eggs/10 ml

A supplemental table including the numbers used to make the chart should be available should modelers or other analysts want to use the exact data.

Table 4. Comparisons of prevalence and intensity at Year 5 among arms.

This table describes the primary outcomes.

|                         | Unadjusted prevalence model estimate (CI) | Adjusted prevalence model estimate (CI) | Unadjusted intensity ratio (CI) | Adjusted intensity ratio (CI) |
|-------------------------|-------------------------------------------|-----------------------------------------|---------------------------------|-------------------------------|
| Study A: Arm 1 v. Arm 2 |                                           |                                         |                                 |                               |
| Study B: Arm 1 v. Arm 2 |                                           |                                         |                                 |                               |
| Study C: Arm 1 v. Arm 2 |                                           |                                         |                                 |                               |

*General approach to analysis:* The general approach is to use mixed models to estimate differences between the arms in year 5 only, analyzing each study separately. We will report unadjusted estimates – with just village, study group and arm fitted in the model – and adjusted estimates – where sex and age are also included in the model. The mixed model will implicitly weight for any villages that were not able to sample 100 9-12 year old children.

ICC will be calculated using mixed models in the primary analysis.

All models will be based on individual level data on 9-12 year old children only.

*Sample code:* The following codes are provided as examples.

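### The 1/n village weight inside the compound-symmetry GEE overshoots equal village weighting: in the adjusted Table 4 models, villages with fewer children gain influence and precision is lost

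*Combined protocol and SAP*

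**What the plan says.** In the multi-country SAP, section VI.b, the general approach under Table 4 commits to adjusted estimates with age and sex, "along with weighting for number of children who provided data, because not all villages were able to sample 100 9-12 year old children". Table 4 is the table of primary outcomes.

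The sample code treats the village as the cluster and states that "we assume compound symmetry within a village". For adjusted prevalence it defines "villweight of individual = 1/# samples collected in village" and adds the statement "weight villweight" to the compound-symmetry GEE. For adjusted intensity, "The code is the same as for the adjusted prevalence, but the distribution and link are changed", and the weight statement appears again. The two unadjusted models carry no weight.

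Section VIII gives the reason: some villages enrolled well below the target of 100, so a village-weight term is added "to weight results according to numbers of children tested per village".

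The Niger SAP uses mixed models. Under its Table 4 it says "The mixed model will implicitly weight for any villages that were not able to sample 100 9-12 year old children". Its adjusted prevalence text nevertheless announces and defines the same 1/n weight, and its section VII repeats the sentence about a weight in a GEE. None of the Niger model code contains a weight statement.

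**The concern.** The weight is meant to deal with unequal numbers of children per village. An exchangeable GEE already does so: it discounts the extra children in a large village according to the within-village correlation. A second factor of 1/n corrects again for something already largely corrected, and the balance tips towards the smallest villages.

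Three things are at stake in the primary-outcome table:

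- The adjusted estimates target no stated average of children or of villages.
- They are less precise than the same model without the weight.
- A gap between the adjusted and unadjusted columns cannot be put down to age and sex, because the weighting changes at the same time.

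**Working it through.** **Inputs from the documents.** Child weight 1/n; exchangeable working correlation with village as cluster; target of 25 villages per arm and 100 children per village. The nominal totals reproduce: 3 × 25 × 100 = 7,500 for Study 1 and 6 × 25 × 100 = 15,000 for Study 2. This confirms the design figures only and does not test the weight.

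**Inputs not given.** Year 5 village sizes in the multi-country studies, and the ICC (rho). Both are assumed below and shown as ranges.

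**Net weight of a village.** A weight w that is constant within a village multiplies that village's inverse working covariance by w. Its total weight in an arm mean is therefore

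w × n/(1+(n-1)rho).

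- No weight (w = 1): n/(1+(n-1)rho). This rises with n and is the efficient weight if rho is right.
- SAP weight (w = 1/n): c(n) = 1/(1+(n-1)rho). This falls with n for any rho > 0.
- w = 1/n with an independence working correlation (rho set to 0): exactly 1 per village.

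**Influence of a 20-child village relative to a 100-child village.** With the SAP weight this is (1+99rho)/(1+19rho):

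- rho 0.05: 5.95/1.95 = 3.05
- rho 0.10: 10.9/2.9 = 3.76
- rho 0.30: 30.7/6.7 = 4.58

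Without the weight, multiply by 20/100: 0.61, 0.75 and 0.92.

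**Variance of an arm mean.** With v(n) proportional to (1+(n-1)rho)/n, the variance under the SAP weight is Σc²v/(Σc)², and the efficient value is 1/Σ(1/v). Worked case, rho 0.05, 20 villages of 100 and 5 of 20 (assumed):

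- c(100) = 1/5.95 = 0.168; c(20) = 1/1.95 = 0.513; Σc = 3.361 + 2.564 = 5.925
- v(100) = 0.0595; v(20) = 0.0975; Σc²v = 0.0336 + 0.1282 = 0.1618
- SAP weight: 0.1618/5.925² = 0.00461
- Unweighted exchangeable GEE: 1/(20/0.0595 + 5/0.0975) = 1/387.4 = 0.00258
- Ratio 1.79, so the standard error is √1.79 = 1.34 times as large

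In this case the five small villages hold 100 of 2,100 children (5%) and carry 2.564/5.925 = 43% of the arm's weight.

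**Range over assumed sizes, 25 villages per arm, rho 0.02 to 0.30:**

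| Assumed sizes | Variance relative to unweighted exchangeable GEE |
|---|---|
| all 100 | 1.00 |
| spread over 50–100 | 1.04 |
| 20 at 100, 5 at 50 | 1.10–1.11 |
| spread over 20–100 | 1.25–1.27 |
| spread over 10–67 (mean 38.5) | 1.35–1.39 |
| 20 at 100, 5 at 20 | 1.73–1.80 |
| 23 at 100, 2 at 10 | 2.2–3.0 |

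The row with mean 38.5 reflects the only size clue for a multi-country study. Section VIII says 52 Mozambique children were 0.9% of those tested in Year 1, so about 52/0.009 = 5,778 were tested, or about 39 per village if there were 150 villages (an assumption). The models use Year 5, so this is indicative only.

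**Check by simulation.** Logistic exchangeable GEE, arm-only model, 25 villages per arm, 2,500 data sets per scenario. Variance ratios were 1.22–1.28 (spread over 20–100), 1.37–1.42 (10–67) and 1.75–1.89 (20 at 100, 5 at 20). In the last case the sandwich test at nominal 5% rejected a true null in 7.7–9.2% of runs with the weight and 5.6–7.0% without. The algebra carries over approximately to the negative binomial model and to models with age and sex.

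**The case against.** **The weight may aim at equal villages.** Neither statement of purpose fixes a direction beyond doubt, and the Table 3 footnote asks for intensity as a mean of village means. On that reading 1/n is the usual equal-village weight. This stands in part. A reader might infer that the weight does the exact reverse of its purpose. That fits the natural sense of the section VIII sentence but is not the only reading. On the equal-village reading the fault is an overshoot, because 1/n gives equal villages only without the exchangeable correlation. The weight misses its target on either reading.

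**The code is only an example.** It is labelled so. But the prose in sections VI.b and VIII commits to weighting, and the 1/n line is its only definition in the multi-country SAP.

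**The published results may not use it.** A reader might infer that small villages dominate Supplemental Tables S1 to S5. The documents do not support that. The table titles name clustering, age and sex but no weight, and the tables report prevalence ratios, whereas the sample code's logit link yields odds ratios.

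**The arm contrast may be unbiased.** The same rule applies in every randomised arm, so a shift in one arm's level does not by itself bias a comparison. If outcome is unrelated to village size, the issue is precision, which the sandwich variance largely reflects. This stands; bias in the contrasts is not shown.

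**The size is assumed.** It is. Niger's Year 5 totals in Table S6 (7,358, 7,361 and 7,413 in Groups A, B and C) would be about 98 per village at an assumed 75 villages each. But Niger's code carries no weight, so this says little about the studies where the weight applies.

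**Conclusion.** The concern holds for the adjusted prevalence and adjusted intensity columns of Table 4 in the multi-country SAP. For any rho > 0 with unequal village sizes, villages with fewer children receive more influence, and the estimate is neither a child average, a village average nor the efficient combination. If all villages have 100 children the weight has no effect; at rho = 0 it gives equal villages.

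The direction follows from the plan's own definitions. The size does not: relative variance runs from 1.00 to about 3 over the assumed sizes, and no single figure, including the 1.8 of the five-small-villages case, should be taken as the trial's loss. The excess type I error was clearest in that same assumed case. The unadjusted columns are unaffected. In the Niger SAP the point is editorial, because the weight appears in its text but not in its code.

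**What to change.** - Delete the weight statement from the adjusted prevalence and adjusted intensity models, keep the exchangeable GEE as primary, and re-run.
- If equal villages are the intended estimand, say so and use 1/n only with an independence working correlation. In the scenarios tried this cost at most 6% in variance for rho of 0.05 or more, and at most 16% at rho 0.02.
- Reconcile the weighting sentences in the multi-country SAP: the general approach under Table 4, the adjusted prevalence text and section VIII.
- Reconcile the Niger text in the same way: Table 4, adjusted prevalence and section VII.
- State whether the weight was used for Supplemental Tables S1 to S5.

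The cost is one line removed from each of two models, a re-run of those models, and a few edited sentences. No new data are needed.
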